**Methods/design:**

The MaDO study is a pre-post-controlled multi-centre study, that is performed in four hospitals in the Netherlands. It includes a pre and post measuring period of six months each with six months of implementation in between in at least 40 patients per hospital per measurement period.

Primary outcome measure is the percentage of patients treated in ultra short stay. Secondary endpoints are the percentage of patients treated according to protocol, degree of involvement of home care nursing, quality of care from the patient's perspective, cost-effectiveness of the ultra short stay programme and cost-effectiveness of the implementation strategy. Quality of care will be measured by the QUOTE-breast cancer instrument, cost-effectiveness of the ultra short stay programme will be measured by means of the EuroQol (administered at four time-points) and a cost book for patients. Cost-effectiveness analysis will be performed from a societal perspective. Cost-effectiveness of the implementation strategy will be measured by determination of the costs of implementation activities.

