#### Exclusion criteria

Concerning surgical techniques, there is no contra-indication for ultra-short stay. Patients whose physiology impedes participation, as assessed by the breast surgeon and breast nurse, are excluded from the study. Patients who cannot rely on sufficient informal care in the home situation during the first night following surgery and patients with complaints that necessitate postoperative monitoring (e.g. cardial, pulmonal or neurological diseases) are scheduled for at least one overnight stay. This decision is made in consultation with the anaesthesiologist. The breast nurse scores the reasons for patients who do not participate.

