### Implementation strategy

The first step in the implementation process concerns the assessment of the guideline recommendations by consensus among experts, who define the complete set of recommendations (n = 29) as well as a set of key recommendations (Table 1).

**Table 1 T1:** Key recommendations of the study guideline to enable ultra short stay for breast cancer surgery. The complete guideline contains 29 recommendations. The participating breast nurses and surgeons from the study groups rated all recommendations and decided upon which recommendations would be defined as 'key' recommendations.

• The treatment of all breast cancer patients is planned in a weekly multidisciplinary meeting.
• The interval between referral and first visit to the breast unit is 5 working days or less.
• The interval between diagnostic tests and informing patients about their results is 5 working days or less.
• The interval between the decision to operate and surgery is 15 working days or less.
• The number of preoperative hospital visits is minimised.
• The general practitioner is informed about diagnosis, treatment plan and potential side-effects prior to surgery.
• Patients planned for day care treatment are postoperatively given the choice between continuation of admission and discharge.
• Information given to patients about discharge is supported by written information.
• Decisions on patient discharge are based on clear guidelines.
• Specialised home care* for patients in the period following surgery is facilitated.
• The breast nurse stays in contact with the patient during the postoperative period.
• At least one night of hospital admission is planned for patients
with co-morbidity and/or insufficient postoperative supervision.
• The breast nurse informs the patient about the need for informal care in the home situation.

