### Statistical analyses

Intention to treat will be used for data analyses, and analyses will be performed using the SPSS package, version 12.0.1 ^® ^for Windows (SPSS INC 1989–2003). P values < 0.05 will be defined as statistically significant. The pre and post comparison of the interval scaled outcome variables will be analysed with a multivariate linear regression model. Apart from the independent variable hospital, other independent variables included in this model are type of surgery, age, informal care at home, involvement of home care nursing and starting time of surgery. Furthermore, correlation of data within a hospital are accounted for by clustered data analysis.

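### Co-morbidity, one of the two patient grounds for planning an overnight stay, is missing from the only covariate list the plan states

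*Protocol article*

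**What the plan says.** Exclusion criteria in the protocol article names two groups who are planned for at least one night. The first is "Patients who cannot rely on sufficient informal care in the home situation during the first night following surgery". The second is given as "patients with complaints that necessitate postoperative monitoring (e.g. cardial, pulmonal or neurological diseases) are scheduled for at least one overnight stay". The same section also allows exclusion on judgement: "Patients whose physiology impedes participation, as assessed by the breast surgeon and breast nurse, are excluded from the study".

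Table 1 under Implementation strategy repeats the pair as a key recommendation. At least one night is planned for patients "with co-morbidity and/or insufficient postoperative supervision".

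Statistical analyses specifies one model: "The pre and post comparison of the interval scaled outcome variables will be analysed with a multivariate linear regression model". Besides hospital, the "independent variables included in this model are type of surgery, age, informal care at home, involvement of home care nursing" and starting time of surgery. No term for co-morbidity or anaesthetic risk appears, and the article states no other adjustment for it.

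The Abstract sets the main endpoint: "Primary outcome measure is the percentage of patients treated in ultra short stay". This is yes or no for each patient. The article names no model for it or for complications.

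Study design describes an uncontrolled pre-post study. Under Programme cost-effectiveness, costs and effects of patients treated before implementation are compared with those of patients treated after it.

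**The concern.** With no concurrent control and different patients in each period, covariate adjustment is the only stated statistical protection against a change in case mix. The list takes up one half of the protocol's own pair of overnight factors and leaves out the other. Co-morbidity is fixed before surgery, so adjusting for it cannot remove any of the programme's effect. It plausibly bears on cost, health-related quality of life, length of stay and complications whatever the programme does.

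A change in mix is possible. The two measurement periods start about 12 months apart (six months of baseline measurement, then six of implementation). The breast nurse recruits patients, helps judge physical fitness for entry and coordinates the programme, so the threshold for entry could move once the programme is running.

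The outcomes most directly affected are the interval-scaled ones, which feed the cost-effectiveness objectives. If the same list were reused for an adjusted analysis of Objective 1, the gap would go with it.

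**Working it through.** **What the list covers**

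| Factor | Ground for overnight stay (Exclusion criteria; Table 1) | In the covariate list (Statistical analyses) |
|---|---|---|
| Insufficient support at home | Yes | Yes, as informal care at home |
| Co-morbidity needing monitoring | Yes | No |

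**Size.** The plan gives no figure on co-morbidity, so there is none to reproduce. The inputs are:

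- Baseline ultra-short-stay rate *b* = 13%. This is the uhM starting rate in Sample size calculations. The four hospitals' own rates are not given, so its use for them is an assumption.
- Co-morbidity prevalence *p* = 20–30% (assumption).
- Shift in prevalence between periods *d* = 10 points (assumption).
- Planned difference = 30 points (Sample size calculations).

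If the programme has no effect, the spurious change is *d* × gap, where gap is the rate in patients without co-morbidity minus the rate in those with it. The gap is largest when no co-morbid patient has ultra short stay. It then equals *b* / (1 − *p*).

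| *b* | *p* | Largest gap | Spurious change for *d* = 10 points | Share of 30 points |
|---|---|---|---|---|
| 13% | 20% | 0.13/0.80 = 16.3 points | 1.6 points | 5% |
| 13% | 30% | 0.13/0.70 = 18.6 points | 1.9 points | 6% |
| 24% | 20% | 0.24/0.80 = 30 points | 3.0 points | 10% |
| 21% | 30% | 0.21/0.70 = 30 points | 3.0 points | 10% |
| 40% | 20% | 0.40/0.80 = 50 points | 5.0 points | 17% |
| 35% | 30% | 0.35/0.70 = 50 points | 5.0 points | 17% |

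The sign follows the shift: a fall in co-morbidity adds these points and a rise subtracts them. Age and type of surgery, where adjusted for, would take out part.

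**Complications.** With an assumed risk gap of 5 to 20 points, the same 10-point shift moves the rate by 0.10 × 5 = 0.5 to 0.10 × 20 = 2 points.

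**Costs and EQ-5D.** The bias before adjustment is *d* times the mean difference between patients with and without co-morbidity. The documents give no such difference, so no amount can be stated.

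**Chance imbalance.** At *p* = 20%, the difference in prevalence between periods has a 95% range of ±1.96 × √(2 × 0.2 × 0.8 / *n*). That is ±17.5 points per hospital (*n* = 40) and ±8.8 points pooled (*n* = 160). This is sampling error, already contained in the standard error of the crude comparison. It is not a bias and is not added to the figures above.

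**Precision.** The share of outcome variance explained is *p*(1 − *p*) × gap² / [*b*(1 − *b*)]. At *b* = 13% it is at most 0.16 × 0.1625² / 0.1131 = 4% for *p* = 20% and 0.21 × 0.1857² / 0.1131 = 6% for *p* = 30%. The gain in precision is modest.

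**The case against.** A reader might infer that the omission leaves the primary outcome and complications confounded, and confounded in favour of Objective 1. The documents do not support that, for four reasons.

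- **Scope of the list.** It is tied to the linear model for interval-scaled outcomes. Admission type and complications are not interval-scaled. The article names no model for them, and a condensed article may leave that to a fuller document. Adding a term to this list would not by itself change their analysis.
- **Definition of ultra short stay.** Under Intervention it includes a stay of up to 24 hours. A patient planned for one night because of co-morbidity can still count as ultra short stay. The rule separates day care from overnight stay more clearly than it separates ultra short stay from a longer stay, so the largest gaps in the table are upper limits.
- **Direction.** Nothing indicates that co-morbidity would fall rather than rise. Patients are consecutive, from the same four hospitals and under the same criteria.
- **Size.** A spurious change of 3 to 5 points needs a baseline of at least 21–24% to 35–40%, well above the only pre-programme rate given.

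There is also partial protection. Age and type of surgery are in the list. Reasons for non-participation and for departing from the ultra short stay protocol are recorded, so a change in selection might be visible. The Discussion concedes that the pre-post design cannot rule out developments in health care, although it does not mention patient mix.

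All of this stands, and it limits the point. It does not explain why one of two paired baseline factors was listed and the other left out. Age is only a partial proxy, and consecutive enrolment does not prevent a change in judgement-based exclusion.

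**Conclusion.** The point holds as a gap in the stated covariate list, not as a demonstrated bias. The list for interval-scaled outcomes includes informal care and omits co-morbidity, although the article treats the two as paired grounds for an overnight stay. A change in co-morbidity mix would be only partly removed and could be read as a programme effect in either direction. This matters most directly for costs and EQ-5D scores, and would extend to ultra short stay and complications if the list were reused there.

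The size is not known from the documents. Assuming a 13% baseline, 20–30% co-morbidity and no programme effect, a 10-point shift moves the ultra-short-stay percentage by at most about 2 points, which is 5–6% of the planned 30-point difference. Without a programme effect, a shift of that size gives more only if the baseline is higher. It is unlikely on its own to produce the planned difference. The change is worth making because it is specific and cheap.

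**What to change.** 1. Record co-morbidity requiring postoperative monitoring (yes/no, or the pre-anaesthetic risk class) before surgery for every patient in both periods, not only as a reason for staying.
2. Add it to the covariates in Statistical analyses for the interval-scaled outcomes.
3. Use the same baseline covariates (hospital, age, type of surgery, co-morbidity) in any adjusted comparison of the ultra-short-stay percentage and of complications, with a model suited to yes/no outcomes.
4. Report co-morbidity prevalence by period and hospital, and give crude and adjusted results side by side.

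The cost is one Case Record Form item, if it is not already there, and one extra model term.

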#### Measurements and timing of measurements (Figure 1)

**Figure 1 F1:**
[figure not shown]
**Overview patient questionnaires**. Overview of the type of questionnaires that are offered to patients and the time at which these questionnaires should be filled out.

- Information on the achievement of the targets of the implementation strategy is collected through Case Record Forms.

- Quality of care is measured from the patient's perspective through the QUOTE-breast cancer, a questionnaire that was developed by and for breast cancer patients and concerns those aspects that breast cancer patients perceive as most important when assessing quality of care[24,25]. The QUOTE-breast cancer questionnaire is filled out six weeks after surgery.

- Information on the performance of professionals is gained through Case Record Forms. The performance indicators have been developed by means of a consensus procedure in the uhM project group.

- Information on societal costs are retrieved from hospital information systems and through a prospective cost book that is filled out by patients during six weeks from the moment of discharge. The day before surgery, patients are asked to fill out a retrospective cost book to assess the patients' health-care related costs for a period of two weeks prior to surgery.

- Patients fill out EuroQol questionnaires at baseline (one day before surgery) and at 24 hours, one week and six weeks after surgery.

When patients sign informed consent and receive the questionnaires, a stamped envelope is given to them which can be used to return the set of questionnaires.

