Programme cost-effectiveness (as compared to care as usual) consists of the two components costs and effectiveness, and is expressed as incremental costs per Quality Adjusted Life Year (QALY) of the ultra short stay programme versus care as usual. Incremental costs are expressed as the difference in costs between the ultra short stay programme and care as usual. Costs are calculated by multiplying the volumes with the appropriate cost prices. Information on (societal) costs are retrieved from hospital information systems and through a prospective cost book that is filled out by patients during six weeks from the moment of discharge. Effectiveness of the programme is determined through the measurement of safety, (number of complications, number of visits to the emergency unit, number of re-admissions etc.; information gained from the Case Record Forms) and generic health-related Quality of Life. Generic health-related Quality of Life is recorded through the EuroQol-5D (EQ-5D)[26], which is completed at baseline, 24-hours after surgery, 1 week after surgery and 6 weeks after surgery. QALYs will be determined in two ways; from a societal perspective using the Dolan score, and from an individual perspective using the VAS score of the EuroQol. The multiple imputation method will be used for missing data analysis[27].

- Policy cost-effectiveness of implementation of the ultra short stay programme versus 'doing nothing' is expressed as incremental costs per Quality Adjusted Life Year (QALY). Costs of the implementation strategy is measured through cost forms that participants in the study groups fill out, through scoring by a researcher ([name]) of all other costs (e.g. times, materials, travel costs) in a data sheet. Effectiveness of the implementation strategy is measured through Case Record Forms containing treatment information. More details on programme cost-effectiveness and policy cost-effectiveness can be found in the section 'Economic evaluation'.

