### Programme cost-effectiveness

The time horizon of six weeks seems appropriate as patients may receive additional treatment after surgery (e.g. radiotherapy, chemotherapy or hormone replacement therapy). Therefore, we expect that only short-term quality-of-life effects and costs can be attributed to the ultra short stay programme. Cost analysis includes health care costs and costs outside health care such as out-of-pocket costs or productivity costs due to reduction in paid work and/or domestic activities. Health care costs refer to hospital and other health care facilities costs. Hospital costs consist of personnel, material, capacity costs, and overhead, associated with the diagnosis, surgical treatment, hospital stay and follow-up. Other healthcare costs include costs of visits to the general practitioner, medication, home care etc. Health care costs are estimated by multiplying the resource utilization with the cost price per unit. Most of these costs are estimated by using existing resource registration systems and available cost prices through the financial departments of the participating centres. If true cost prices are not available in the participating centres, 1) existing cost prices of the uhM or 2) official directive prices are used[28]. Healthcare costs incurred outside the hospital and costs outside health care are partly estimated through a structured cost book that is kept by all participating breast cancer patients during the period of six weeks following discharge. Productivity losses due to absence from work are estimated through the friction cost method[28,29]. To perform the cost-effectiveness analysis, costs and effects of patients treated according to care as usual (before implementation) will be compared to costs and effects of patients treated according to the ultra short stay programme (after implementation).

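### The listed covariates omit pre-surgery paid-work status, which costs precision in the productivity-cost comparison and leaves any real employment shift between periods only partly adjusted, through age

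*Protocol article*

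**What the plan says.** Under Statistical analyses, the protocol article states: "The pre and post comparison of the interval scaled outcome variables will be analysed with a multivariate linear regression model". Hospital is one independent variable; the others "are type of surgery, age, informal care at home, involvement of home care nursing and starting time of surgery". Costs are not named as an outcome of this model.

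The cost side is described elsewhere. Under Programme cost-effectiveness, the costs outside health care include "productivity costs due to reduction in paid work and/or domestic activities", and one part of these has a stated valuation method: "Productivity losses due to absence from work are estimated through the friction cost method". The same section gives the contrast: "costs and effects of patients treated according to care as usual (before implementation) will be compared to costs and effects" of patients treated after implementation. Under Measurements and timing of measurements, the increment is defined without an adjustment model: "Incremental costs are expressed as the difference in costs between the ultra short stay programme and care as usual".

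The only cost measurement before surgery is a "retrospective cost book to assess the patients' health-care related costs for a period of two weeks prior to surgery". As described, it gives no baseline for work.

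**The concern.** Within a six-week horizon, the work-absence component is zero for a patient without a job and possibly substantial for one with a job. Whether a patient has paid work, and for how many hours, is therefore likely to be the strongest single predictor of that component. The two cohorts contain different patients and nothing in the design balances employment between them. Age, which is listed, is an imperfect proxy: not everyone below pension age works, and hours differ.

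Two things are at stake. First, variation in work status that could be explained remains in the residual, so the interval for the productivity-cost difference, and to a lesser extent for the societal-cost difference, is wider than it need be. Second, if the share of workers really changed between periods, the resulting cost difference would be attributed to the programme except where age absorbs it. Both pass into the programme and policy cost-effectiveness results.

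**Working it through.** The document gives no figure for productivity costs or for the share of patients in paid work, so there is no stated figure to reproduce. The only input from the plan is the sample size: 40 per hospital per period in four hospitals, so 4 x 40 = 160 per period. The Abstract makes this a minimum.

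**Assumed inputs**
- p, share in paid work: 0.30-0.50.
- a, proportion of the variance in work status explained by age: 0.30-0.50.
- m, mean work-absence cost per worker: scaled to 1,000 units, because no price or hours are given.
- s, SD of that cost among workers: m/2.
- Non-workers: zero. This holds by definition for the work-absence component, but not for productivity cost as a whole.

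**Step 1: what chance alone does.** The SD of the difference in worker share is sqrt(2p(1-p)/n).
- n = 160, p = 0.30: sqrt(2 x 0.30 x 0.70/160) = 0.051.
- n = 160, p = 0.50: sqrt(2 x 0.50 x 0.50/160) = 0.056.

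So differences of 5 points are ordinary, and the 95% range is about +/-10 to 11 points.

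**Step 2: is that bias?** A simulation used 4,000 runs per scenario, 160 per cohort, no true effect, cost in workers only and no age term, with p = 0.3 or 0.5 and s/m = 0.3, 0.5 or 0.8.
- Without work status: mean error -0.9 to 1.3 units, SD of the estimate 55-85, coverage of the 95% interval 94.7-95.4%.
- With work status: mean error -2.0 to 0.5 units, SD 18-62, coverage 94.5-95.8%.

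Both analyses are unbiased with correct coverage. Only the spread changes.

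**Step 3: precision gained beyond age.** The share of the residual variance due to work status is p(1-p)m²(1-a) / [p(1-p)m²(1-a) + p s²]. With s = m/2 this becomes (1-p)(1-a) / [(1-p)(1-a) + 0.25]. The standard error falls by 1 - sqrt(1 - share).
- p = 0.3, a = 0.3: share 0.49/0.74 = 0.66; reduction 0.42.
- p = 0.3, a = 0.5, or p = 0.5, a = 0.3: share 0.35/0.60 = 0.58; reduction 0.35.
- p = 0.5, a = 0.5: share 0.25/0.50 = 0.50; reduction 0.29.

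As a check, setting a = 0 gives 0.49 (p = 0.3) and 0.42 (p = 0.5). The simulation at s/m = 0.5 gives 1 - 30.1/59.5 = 0.49 and 1 - 40.4/67.5 = 0.40, in good agreement.

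**Step 4: sensitivity to s.** The 0.25 is (s/m)², so the result depends on it.
- s/m = 0.8, p = a = 0.5: share 0.25/(0.25 + 0.64) = 0.28; reduction 0.15.
- s/m = 0.3, p = a = 0.3: share 0.49/(0.49 + 0.09) = 0.84; reduction 0.61.

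**Step 5: a real shift.** If the true share of workers differed by d between periods, the unadjusted mean cost would move by d x m. For illustration, d = 0.05 gives 0.05 x 1,000 = 50 units per patient. Unlike the error in step 1, this does not shrink with more patients and the interval does not allow for it. Age would remove the part of the shift that runs through age. The document gives no value for d and does not show that it differs from zero.

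**The case against.** The strongest reply has four parts.

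**Chance imbalance is already accounted for.** This stands. A reader might infer that a chance difference in the share of workers would be misread as a programme cost or saving. Step 2 shows otherwise: the estimate is centred on the truth and the interval covers at its nominal rate. What is lost is precision.

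**Productivity costs do not arise only in workers.** This also stands. The article counts reduced domestic activities too, so a patient without a job can contribute. The calculation therefore applies to the work-absence component. Domestic losses in non-workers would narrow the gap between the groups and reduce the gain for productivity cost as a whole.

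**The regression is not shown to be the cost model.** It is true that Statistical analyses does not name costs, and that a condensed article may leave the economic model to a fuller document. But costs are interval scaled, no other model is named, and the alternative reading, a plain difference between cohorts, adjusts for nothing. Work status is missing on either reading. The point concerns a list that the article does state.

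**No systematic shift is demonstrated.** Correct. Consecutive patients from the same four hospitals are eligible in both periods, and the Discussion acknowledges the limits of a pre-post design. Still, questionnaires depend on returned consent, and exclusion rests partly on the judgement of surgeon and breast nurse, so the case mix could change. This supports a safeguard, not a claim that bias exists.

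**Conclusion.** The point holds as a matter of precision and protection. Pre-surgery paid-work status is a strong predictor of one cost component, it is absent from the stated covariates, and age covers it only partly. With 30-50% working, age explaining 30-50% of work status, no work-absence cost in non-workers and a within-worker SD of half the mean, adding it would reduce the standard error of the work-absence component by about 29-42%. Varying that SD from 0.3 to 0.8 of the mean widens the range to roughly 15-61%. All these inputs are assumptions. The gain for total societal cost, and for cost per QALY, is smaller and not quantified, because the document does not show how large work absence is relative to other costs.

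The document does not support saying that the planned cost comparison is biased or its interval invalid on this account; that would require a real change in employment between periods, for which there is no evidence. Severity: optional low-cost improvement.

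**What to change.** Add pre-surgery paid-work status (yes/no, with contracted hours) to the independent variables for the productivity-cost and total societal-cost comparisons. If these comparisons are not meant to fall under the regression in Statistical analyses, state the covariate where the cost comparison is specified. Report the share in paid work in each period, so that readers can judge whether the cohorts are comparable in this respect.

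Record the employment contract and hours, not attendance at work just before surgery. The programme cannot plausibly change the former, so adjusting for it removes no programme effect.

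The cost is one more covariate and the need to record work status for every patient, including those without a job. Work status is needed in any case to value absence from work. No extra patients or visits are required.
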